## • Outcome Measures

### A. Primary outcome measure

QOL questionnaire: SGRQ (St. George's Respiratory Questionnaire) Total domain in Japanese version.

\*Main evaluate the difference one year (52 weeks) after the baseline.

\*The SGRQ assessment is obtained by patients' filling in the paper-format questionnaires in a hospital room where no research-related personnel around, and the questionnaires are

collected by hospital staff unrelated to the study.

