In this study, we perform the analysis without imputing missing values in the main analysis. In addition, as a post hoc sensitivity analysis, analysis of covariance will be performed with multiple imputation for the primary and secondary outcome measures, including missing data for dropouts. For dropout cases, multiple imputation is performed assuming MAR (Missing At Random), and when doing so, variables that exhibit a correlation ( $>0.5$ ) with the baseline values of each evaluation item and the missing variables are used as auxiliary variables.

All main analyses are carried out with STATA-16 (StataCorp LLC, College Station, TX, USA).

All data are entered by an independent data entry personnel not involved in the study.

A combination of machine-generated alphabet letters was assigned to each patient and then the data were randomized so that the individual patient cannot be identified in the data without the collation list. Furthermore, no patient information will be revealed to all

those involved in the study until the statistical analysis is complete.

The statistician must perform the analysis with the grouping and patient information masked.

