#### • Sample Size

1. The target number of cases is 44.
2. The sample size was found using the test of difference (two-sided) in the mean value of the difference of SGRQ (Total domain) values between before and after 52weeks of the acupuncture treatment from our preceding research results. Considering the results of our preceding research and the report on Minimal clinically importance (MCID) of SGRQ (total domain) as 4 units, setting the absolute value of the difference to be detected as 10 units, standard deviation(SD)10.0, the significance level as 0.05, and power as 0.8, the sample sizes per group was calculated to be 17 (two groups 34). This trial considers clinical effects for one year long, a certain number of dropouts is expected. Therefore, assuming approximately 30 percent (10 cases) may drop out, about 22 cases for each group is necessary (the final sample size was 44).

Table Sample size (two groups)

| $\tau$ | Power (%) | Standard deviation |     |      |      |
|--------|-----------|--------------------|-----|------|------|
|        |           | 9                  | 9.5 | 10.0 | 10.5 |
| 10     | 90        | 37                 | 40  | 45   | 49   |
|        | 80        | 28                 | 31  | 34   | 37   |
|        | 70        | 23                 | 25  | 27   | 30   |
|        | 60        | 18                 | 20  | 22   | 24   |
|        | 50        | 15                 | 16  | 18   | 20   |

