### Criteria of Intervention Cancellation

Cases to be considered as intervention cancellation

1. when a patient requests to stop acupuncture treatment
2. when the physician in charge considers further acupuncture treatment is not appropriate (including the request from patient).
3. When a patient is hospitalized due to the acute aggravation of COPD or other reasons and intervention by acupuncture treatment becomes difficult, the physician in charge or the main researcher can cancel the intervention.
4. When an acupuncture treatment facility collaborating with this research cannot

continue acupuncture treatment, the main researcher can cancel the intervention.

- **Procedure of Trial Stoppage (cancellation)**

1. During the trial period, in case the physician in charge recognizes that the safety of acupuncture treatment cannot be secured, the main researcher shall be consulted and can decide to cancel the trial.
2. If the cancellation of the trial is decided, all who are involved in this trial should be notified within one week and the trial is cancelled.

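### The protocol's one analysis that restores dropouts assumes MAR, so it cannot test loss of benefit in acupuncture dropouts beyond what their observed data already show

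*Protocol*

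**What the plan says.** The primary outcome is the change in SGRQ total (Outcome Measures, A: "Main evaluate the difference one year (52 weeks) after the baseline"). Under Statistical Analysis, the FAS is every assigned patient except dropouts. The PPS also excludes dropouts and requires at least 40 treatments. The main analysis is done without imputation.

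A further ANCOVA after multiple imputation, covering the primary and secondary outcomes and labelled post hoc, puts dropouts back: "For dropout cases, multiple imputation is performed assuming MAR (Missing At Random". Its auxiliary variables are "variables that exhibit a correlation ( $>0.5$ ) with the baseline values of each evaluation item" and with the variables that are missing. No other analysis of dropouts is described.

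The Sample Size section expects about 10 dropouts and sets enrolment at 44, without saying how dropouts divide between the arms. Criteria of Intervention Cancellation lists four reasons for ending acupuncture: patient request, physician judgement, closure of a treatment facility, and a hospital stay ("When a patient is hospitalized due to the acute aggravation of COPD or other reasons and intervention by acupuncture treatment becomes difficult"). The protocol does not define dropout. It also does not say whether a patient who stops acupuncture is still assessed at week 52.

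**The concern.** A sensitivity analysis is useful when it relaxes an assumption that the main analysis depends on. Here the completer analysis takes those who left to be like those who stayed, given arm and covariates, and MAR imputation takes much the same. An acupuncture patient who leaves is given the response of similar acupuncture patients who completed. If those who left had lost their benefit by week 52 and nothing observed showed it, both analyses would agree and both would overstate the difference among all randomised patients.

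Patients and acupuncturists are unblinded, and close to a quarter of those randomised are expected to drop out, so this departure deserves a direct test. Without one, agreement between the two analyses says little about informative dropout.

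**Working it through.** **The plan's own figure.** Inputs from Sample Size: "The sample size was found using the test of difference (two-sided", "setting the absolute value of the difference to be detected as 10 units", "standard deviation(SD)10.0, the significance level as 0.05, and power as 0.8".

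- Normal approximation: n per arm = 2 × (1.96 + 0.84)² × 10² / 10² = 15.7, so 16.
- Two-sample t-test (noncentral t): 16.7, so 17 per arm, with power 0.807 at 17.

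The second matches "the sample sizes per group was calculated to be 17 (two groups 34". Adding 10 dropouts gives 44, or 22 per arm. Ten is 10/44 = 22.7% of those randomised and 10/34 = 29.4% of those evaluable.

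**Dilution if acupuncture dropouts lose all benefit.** Assumptions: the completer difference is 10; acupuncture dropouts have the usual-care mean at week 52; usual-care dropouts resemble usual-care completers. The split of the 10 dropouts is not in the protocol, so three are shown. With d acupuncture dropouts:

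- all-randomised difference = 10 × (22 − d)/22
- half-width of the 95% CI = t(0.975, 32 df) × 10 × √(1/n_A + 1/n_U), with t = 2.037 and n_A, n_U the observed patients per arm

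| Dropouts, acupuncture/usual care | Observed n_A/n_U | Difference | Half-width | 95% CI | Shortfall from 10 |
|---|---|---|---|---|---|
| 5/5 | 17/17 | 10 × 17/22 = 7.7 | 6.987 | 0.7 to 14.7 | 2.3 |
| 7/3 | 15/19 | 10 × 15/22 = 6.8 | 7.035 | -0.2 to 13.9 | 3.2 |
| 10/0 | 12/22 | 10 × 12/22 = 5.5 | 7.310 | -1.9 to 12.8 | 4.5 |

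The quoted MCID is 4 units. The intervals are approximate because they keep the complete-case standard error. If the dilution were treated as a known multiplier, the standard error would shrink by the same factor and the test statistic would not move. The fall in the estimate does not depend on that choice.

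**What each imputation returns.** A simulation used 22 per arm, effect 10, SD 10, the same loss of benefit, 1,500 replicates, 20 imputations and Rubin's rules. The imputation model held arm and baseline only. Each cell gives the mean difference and the share of runs significant at 0.05.

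| Split | Completers | MAR imputation | Jump-to-control imputation | All 44 observed |
|---|---|---|---|---|
| 5/5 | 10.09; 82% | 10.07; 80% | 7.81; 59% | 7.83; 68% |
| 7/3 | 10.05; 80% | 10.05; 78% | 6.86; 41% | 6.87; 55% |
| 10/0 | 10.10; 78% | 10.09; 74% | 5.49; 14% | 5.52; 37% |

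MAR imputation reproduces the completer result. Jump-to-control recovers the true difference, with conservative significance rates.

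**Effect of week-12 SGRQ.** Suppose a 5/5 split, week-12 values observed for dropouts, benefit already fully lost by then, equal SDs, and a week-12 to week-52 correlation r. MAR imputation then gives 7.73 + 10 × (1 − r) × 5/22. At r = 0.5 this is 8.9 and at r = 0.8 it is 8.2, against a truth of 7.7. Loss arising after the last visit is not captured.

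**Illustrative tipping point.** With the same standard errors, significance is lost once delta, the worsening applied to acupuncture dropouts, exceeds (10 − half-width) × 22/d:

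- 5/5: 3.013 × 22/5 = 13.3
- 7/3: 2.965 × 22/7 = 9.3
- 10/0: 2.690 × 22/10 = 5.9

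Total loss of benefit is delta = 10. It does not tip the 5/5 case but does tip the other two.

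**The case against.** The strongest reply is that methods for data not missing at random are commonly left to the statistical analysis plan, which is not at hand and may contain them. That limits the claim to this document. It does not remove it, because the protocol itself fixes the check, its assumption and its auxiliary rule.

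Several stronger readings might be inferred, and the documents do not support them:

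- **That MAR imputation must return about 10 whatever happens.** SGRQ is measured at week 12 and may qualify as an auxiliary, in which case part of a loss already visible then is picked up.
- **That the cancellation criteria show informative missingness confined to the acupuncture arm.** They are reasons for stopping acupuncture, not for a missing SGRQ. Usual-care patients can also withdraw or be hospitalised, and closure of a facility has no obvious link to outcome. The criteria make MAR doubtful but do not show that it fails.
- **That the auxiliary rule discards strong negative correlations.** The threshold has no absolute-value sign, but it can be ordinary shorthand for strength. It is an ambiguity to clear up.
- **That the trial's conclusion would be overturned.** With an even split and total loss, the interval still excludes zero, and all three diluted estimates stay above the 4-unit MCID.

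It is also fair that 44 patients support few auxiliary variables, and that the exacerbation diary, handed in only after the study period, may not exist for dropouts.

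**Conclusion.** The point holds for this protocol as written: its only stated analysis that includes dropouts cannot test unobserved loss of benefit among those in the acupuncture arm. Under total loss, the all-randomised difference would be 5.5 to 7.7 units where completers show 10, a shortfall of 2.3 to 4.5 units. The approximate interval crosses zero in the 7/3 and 10/0 splits but not in the 5/5 split.

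These figures rest on assumed splits, an assumed extreme of no retained benefit, the planning SD of 10 and the complete-case standard error. They show what the planned check could miss, not what happened. The matter is worth correcting, but it concerns a sensitivity analysis and leaves the primary estimator as it is. Excluding dropouts from the FAS is a separate and larger question, and it is why this check carries so much weight.

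**What to change.** For the 52-week SGRQ total, pre-specify a control-based (jump-to-control) or delta-adjusted imputation of acupuncture-arm dropouts, and report the delta at which the conclusion changes. State the variance method with it, since significance under control-based imputation depends on it.

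In the MAR model:

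- always include arm, baseline value, week-12 SGRQ where observed, and GOLD stratum;
- write the auxiliary rule as |r| > 0.5;
- add a predictor of dropout, such as recorded hospitalisation, only where it is available for dropouts and 44 patients can support it.

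The cost is a few more imputation runs on existing data and a short addition to the text. The downside is that the statement on robustness may turn out less favourable.

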### 3.Preparation of the statistical analysis report.

After all of the case-handling is done and data are fixed, statistical analyses are performed and the statistical analysis report is prepared.

#### • Sample Size

1. The target number of cases is 44.
2. The sample size was found using the test of difference (two-sided) in the mean value of the difference of SGRQ (Total domain) values between before and after 52weeks of the acupuncture treatment from our preceding research results. Considering the results of our preceding research and the report on Minimal clinically importance (MCID) of SGRQ (total domain) as 4 units, setting the absolute value of the difference to be detected as 10 units, standard deviation(SD)10.0, the significance level as 0.05, and power as 0.8, the sample sizes per group was calculated to be 17 (two groups 34). This trial considers clinical effects for one year long, a certain number of dropouts is expected. Therefore, assuming approximately 30 percent (10 cases) may drop out, about 22 cases for each group is necessary (the final sample size was 44).

Table Sample size (two groups)

| $\tau$ | Power (%) | Standard deviation |     |      |      |
|--------|-----------|--------------------|-----|------|------|
|        |           | 9                  | 9.5 | 10.0 | 10.5 |
| 10     | 90        | 37                 | 40  | 45   | 49   |
|        | 80        | 28                 | 31  | 34   | 37   |
|        | 70        | 23                 | 25  | 27   | 30   |
|        | 60        | 18                 | 20  | 22   | 24   |
|        | 50        | 15                 | 16  | 18   | 20   |

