#### • **Statistical Analysis**

1. Handling of cases and target group for analysis

In this study, cases enrolled in clinical trials and excluding dropouts will be the main analysis group.

2. Method of analysis

In this study, based on data analysis is performed by setting two analysis groups, FAS (Full Analyze Set) and PPS (Per Protocol Set).

FAS and PPS are defined as follows.

FAS: All assigned patients except for dropped out patients

PPS: Patients who achieved 40 or more acupuncture treatments in one year, excluding dropout patients.

Distributions of all the outcome measures at baseline are shown.

For the primary outcome measures, the secondary outcome measures, and other outcome measures, ratios or means of the differences between baseline and 12 weeks and between baseline and 52 weeks are calculated.

For all outcome measures, we look at the changes of variables in 12 weeks (from baseline to 12 weeks later) and in 52 weeks (from baseline to 52 weeks later). And then, for main outcome measure and secondary outcome measures, we compare these 12-week-change and 52-week-change using the analysis of covariance (ANCOVA) with baseline values and GOLD classification as covariates and treatment group as the factor of interest.

For the change from baseline in other outcome measures, an independent sample t-test is use.

Continuous variables and ordinal variables are shown as the means (standard deviation), and their significant differences are shown by 95% confidence intervals (CI) and p-values (significance level 0.05). Count variables are shown as the number of counts and percentages, and X2 test or Fisher's exact test results are shown with p-values (significance level 0.05).

For the changes in arterial blood oxygen saturation and in pulse during the 6-minute walk, we use the mixed effects model to analyze the difference between the 12-week-change and 52-week change. In this mixed effects model, the fixed effects are groups and times, the interaction terms are group x time, the intercept of random effects is individual, the slope is time, and the estimation method is the maximum likelihood method.

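### The dropout allowance is added to 34 instead of divided out: at the stated 30% dropout, 44 patients leave about 31, and power is about 75–77%, not 80%

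*Protocol*

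**What the plan says.** In the protocol's Section 6, Sample Size, the calculation is a two-sided comparison of the two groups on the mean 52-week change in SGRQ total score. The inputs are given as "setting the absolute value of the difference to be detected as 10 units" and "standard deviation(SD)10.0, the significance level as 0.05, and power as 0.8". From these, "the sample sizes per group was calculated to be 17 (two groups 34"). The allowance for dropout follows: "assuming approximately 30 percent (10 cases) may drop out, about 22 cases for each group is necessary (the final sample size was 44"). A table under the text gives total sample sizes for a 10-unit difference at several SDs and power levels; its entry for SD 10.0 and 80% power is 34.

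Section 6, Statistical Analysis, settles what happens to dropouts: "cases enrolled in clinical trials and excluding dropouts will be the main analysis group". The full analysis set is defined the same way. The main analysis is done without imputation, and multiple imputation appears only as a sensitivity analysis.

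**The concern.** A dropout rate applies to the patients who are enrolled. To finish with 34 when 30% are lost, one divides 34 by 0.7. The protocol instead takes 30% of 34, rounds it to 10, and adds it. The sentence therefore gives a rate and a count that disagree once both refer to the 44 enrolled.

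This bears on the primary endpoint. Every dropout leaves the main analysis set and nothing is imputed in the main analysis, so the number of completers is the sample size of the primary test. Someone interpreting a null result would take the trial to have had 80% power after 30% dropout, when the protocol's own inputs give somewhat less.

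**Working it through.** **Inputs, all from the protocol.** Difference δ = 10, SD σ = 10, two-sided α = 0.05, target power 0.80, 34 evaluable, dropout about 30% or 10 cases, 44 enrolled (Sample Size). Allocation is 1:1 (Random allocation). Dropouts are excluded and not imputed in the main analysis (Statistical Analysis).

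**Step 1: reproduce the evaluable number.** For a two-sample t-test, power = P(|T| > t), where t is the 0.975 quantile on n₁ + n₂ − 2 degrees of freedom and T is noncentral t with noncentrality δ / (σ√(1/n₁ + 1/n₂)). With 17 + 17 the noncentrality is √8.5 = 2.92 and power is 0.807. The smallest total reaching 0.80 is 34, as stated. The same method reproduces all 20 cells of the protocol's table, so it is the right yardstick for what follows.

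**Step 2: reproduce the enrolled number.**

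| Route | Result |
|---|---|
| 34 × 1.3 | 44.2 |
| 34 + 10 | 44 |
| 34 / (1 − 0.30) | 48.6, i.e. 49, or 50 with equal arms |

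Only the first two give 44. The base used for the percentage shows in the count: 10/34 = 29.4%, whereas 10/44 = 22.7%.

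**Step 3: what 44 leaves at 30% dropout.** 44 × 0.7 = 30.8, or 15.4 per group, against the 17 per group required.

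**Step 4: power for the remaining patients (δ/σ = 1).**

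| Evaluable | Dropout from 44 | Noncentrality | Power |
|---|---|---|---|
| 17 + 17 = 34 | 10/44 = 22.7% | √8.5 = 2.92 | 0.807 |
| 15 + 16 = 31 | 13/44 = 29.5% | √(240/31) = 2.78 | 0.767 |
| 15 + 15 = 30 | 14/44 = 31.8% | √7.5 = 2.74 | 0.753 |

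The protocol's table says the same without any new calculation: at SD 10.0, 27 patients give 70% and 34 give 80%, and 31 lies between them.

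**Step 5: let the number of dropouts vary.** If each of the 44 drops out independently with probability 0.30 (an assumption added here), the chance of keeping 34 or more is 0.19, and power averaged over the possible outcomes is about 0.757.

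**Step 6: check the correct inflation.** Fifty enrolled leaves 50 × 0.7 = 35; with 17 + 18 power is 0.819.

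**The case against.** Four points can be made for the protocol.

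- **The count works.** The sentence gives 10 cases as well as 30%, and 44 − 10 = 34 exactly, with power 80.7%. This stands. If the count governs, the target is met, and the fault is that the percentage beside it is wrong for the 44 enrolled. But a reader who relies on the percentage is misled, and 22.7% is not approximately 30%.
- **The deficit is small beside the uncertainty in the SD.** The protocol's table gives 31 as the total for 80% power at SD 9.5, so half a unit on an assumed SD would cancel the shortfall. Also, the whole number nearest to 30.8 is 31, which puts power nearer 77% than 75%. Both remarks are fair and limit how much weight the point carries.
- **The primary analysis is ANCOVA, not the test that was sized.** Adjusting for baseline could recover the loss. If the correlation between baseline and change were 0.3, the residual SD would be 10 × √(1 − 0.09) = 9.54 and power at 15 + 16 about 80.5%; at 0.5 it would be about 87%. The protocol gives no such correlation and takes no credit for it, so this gain is conjecture. It also does not mend the inflation step.
- **Nothing else changes.** Bias, type I error and the analysis are untouched. That is true, and it is why a correction of the text is enough.

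**Conclusion.** The concern holds. The enrolled number comes from multiplying by 1.3 where division by 0.7 was needed. At 30% dropout among the 44 enrolled, 30 or 31 patients remain and power is about 75–77%, some 3 to 5 points below the stated 80%. This rests on the protocol's own difference, SD and significance level, on an unadjusted two-sample t-test, and on near-equal dropout in the two groups. The 80% figure is right only if at most 10 of 44, about 23%, drop out. The effect is modest, but the statement is wrong as written and concerns the primary endpoint.

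**What to change.** Keep 44 and correct the sentence in Sample Size. Recruitment was scheduled to close in October 2018 and the data to be complete in February 2020, so adding patients is not a realistic remedy. Suggested text:

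> Randomising 44 patients (22 per group) leaves the required 34 evaluable if no more than 10 of the 44 (23%) drop out. At 30% dropout about 31 would remain, and power for a 10-unit difference with SD 10 would be about 75–77% (two-sample t-test, two-sided α 0.05, no allowance for covariate adjustment).

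The cost is one sentence and a slightly less favourable power statement. No extra patients are needed and the analysis does not change. Had 30% been meant as the planning rate among those enrolled, the enrolment figure would have been 50 (25 per group).

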### Criteria of Intervention Cancellation

Cases to be considered as intervention cancellation

1. when a patient requests to stop acupuncture treatment
2. when the physician in charge considers further acupuncture treatment is not appropriate (including the request from patient).
3. When a patient is hospitalized due to the acute aggravation of COPD or other reasons and intervention by acupuncture treatment becomes difficult, the physician in charge or the main researcher can cancel the intervention.
4. When an acupuncture treatment facility collaborating with this research cannot

continue acupuncture treatment, the main researcher can cancel the intervention.

- **Procedure of Trial Stoppage (cancellation)**

1. During the trial period, in case the physician in charge recognizes that the safety of acupuncture treatment cannot be secured, the main researcher shall be consulted and can decide to cancel the trial.
2. If the cancellation of the trial is decided, all who are involved in this trial should be notified within one week and the trial is cancelled.

